#### Self-report measures for exploratory subgroup analyses

These measures will additionally be used for exploratory subgroup analyses of the effects of the intervention.

General subjective feelings of social support are measured with the short version of the Social Support List (SSL-6) [81], consisting of 6 items (4-point scale) about the amount of different types of support one receives (range 6–24). Additionally, 6 items assess the satisfaction with the amount of received support (range 6–24). The list has good construct validity and high reliability [81].

Attachment style is measured using the Experiences in Close Relationships Scale (ECR) [82] which dimensionally measures attachment anxiety (18 items) and attachment avoidance (18 items) (7-point Likert scale). Scores range between 18–49 for both subscales, with higher scores indicating a more anxious or avoidant attachment style. The questionnaire has a high reliability and validity [83].

Coping strategy is measured with the Dutch Brief Coping Strategy Indicator (DUBRISCI), a brief version of the Coping Strategies Indicator (CSI) [84]. The questionnaire consists of 9 items (3-point scale), to assess 3 basic modes of coping: problem solving, seeking social support, or avoiding the event (range 0–18). The CSI has been found to be valid and reliable [84].

Peritraumatic dissociation is assessed with the Peritraumatic Dissociation Experience Questionnaire (PDEQ) [85] and uses 10 items of peritraumatic dissociative reactions to a traumatic event on a 5-point scale (range 10–50). The PDEQ is valid and reliable [86].

History of potential childhood trauma is assessed with the short version of the Early Trauma Inventory-Self report (ETI) [87]. The 27-item questionnaire assesses the number and frequency of different types of potentially traumatic experiences (physical, sexual, and emotional abuse and general traumas) and has been shown to be a valid and reliable measure of early trauma.

### Biological measures - Psychophysiology

Heart rate (HR) and heart rate variability (HRV) are assessed with the Polar RS800CX (wrist watch and chest strap). R-R intervals obtained from the equipment will be used to calculate high-frequency HRV (HF-HRV) as an index for parasympathetic nervous system functioning [88].

### Biological measures - blood and saliva

#### Neuroendocrine measures

DHEAS and cortisol are HPA-axis indices and can be determined in saliva. We will use Salivettes (Salivettes, Sarstedt, Rommelsdorf, Germany) for the assessment of DHEAS and cortisol at T2 and T4 (under resting conditions). In addition, to assess normal circadian cortisol levels and cortisol suppression by dexamethasone (DEX) from saliva, participants are instructed to collect 5 saliva samples per day on 2 consecutive days prior to the start of the intervention (time points: at awakening, +15, +30, and +60 minutes after awakening and in the evening before going to bed). Basal cortisol levels are assessed during the first day of saliva collection. A low dose (0.25 mg) of dexamethasone (DEX) is administered at 11:00 pm during the first day [89], to measure cortisol levels after suppression with DEX on the second day.

To assess retrospective cortisol levels, cortisol levels are measured in hair [90]. Fifteen mg of hair is collected at T4. Focus will be on the first 2 1 cm segments of scalp-nearest samples, representing the month prior to trauma, the month after the intervention, and a time period in between.

Saliva samples will be stored at -20°C and hair samples at room temperature until further analysis.

Oxytocin and AVP concentrations will be measured in plasma. Blood samples are collected in 2 ice-chilled 6 ml EDTA tubes, placed on ice immediately after sampling, centrifuged at 4°C within 60 minutes after blood collection and stored until further analysis. Extracted plasma will be stored at -80°C until further analysis.

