**Methods/Design:**

In this multicenter double-blind randomized placebo-controlled trial we will recruit 220 Emergency Department patients at increased risk of PTSD. Trauma-exposed patients are screened for increased PTSD risk with questionnaires assessing peri-traumatic distress and acute PTSD symptoms within 7 days after trauma. Baseline PTSD symptom severity scores and neuroendocrine and psychophysiological measures will be collected within 10 days after trauma. Participants will be randomized to 7.5 days of intranasal oxytocin (40 IU) or placebo twice a day. Follow-up measurements at 1.5, 3 and 6 months post-trauma are collected to assess PTSD symptom severity (the primary outcome measure). Other measures of symptoms of psychopathology, and neuroendocrine and psychophysiological disorders are secondary outcome measures.

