#### Study procedures

After verbal and written informed consent, participants will receive a pre-intervention assessment (T1) for an extensive check of in- and exclusion criteria and to collect baseline characteristics (i.e. current PTSD symptoms, history of and current other psychopathologies, demographics, and several questionnaires assessing psychological functioning). Only those participants eligible for further participation will be randomized. At home, participants will collect saliva samples for the assessment of the cortisol awakening curve and dexamethasone suppression test on 2 consecutive days. During a second appointment (T2), baseline measures of basal psychophysiological functioning are determined. Venous blood and saliva is collected for the analysis of neuroendocrine and (epi)genetic material. Subsequently, participants receive instructions on how to use the nasal spray and will apply the first dose in the presence of the researcher. Two weeks after the start of the intervention, participants receive an online questionnaire to assess psychological functioning (T3).

One month after the end of the intervention (T4) (i.e. approximately 1.5 month post-trauma) the severity of PTSD and the presence of other psychopathology symptoms are assessed. Additionally, blood, saliva, hair, and psychophysiological measures are collected. At the remaining follow-up sessions at 3 (T5) and 6 months (T6) after the index trauma, the severity of PTSD and the presence of other psychopathology symptoms will be re-assessed and a subset of questionnaires will be re-administered.

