#### Intervention

Participants will be blindly allocated to either intranasal oxytocin (Syntocinon®, 40 IU/ml, registered in the Netherlands as RVG 03716) or placebo (Sodiumchloride (NaCl) nasal spray 0.8% based on the Formulary of Dutch Pharmacists). The bottles are re-labeled so that the oxytocin and placebo bottles appear identical. All study medication is prepared by the hospital pharmacy of the Slotervaart Hospital, Amsterdam, under Good Manufacturing Practice (GMP) licence. Participants receive a total of 120 ml of nasal spray, divided over 3 bottles.

Participants are instructed to self-apply a total of 15 doses of 10 puffs of their allocated treatment, i.e. 40 IU oxytocin per dose for the oxytocin condition. A dose of 40 IU twice a day is comparable to the doses previously used in human studies investigating effects of multiple treatments of oxytocin [61,62] and does not produce significant side effects or adverse outcomes [63]. The first intranasal dose is self-applied under researcher supervision at the latest on day 10 post-trauma exposure (T2). The following 14 doses will be administered in the morning and evening of the 7 consecutive days, preferably with 12-hour time intervals. Participants are asked to keep a medication diary to register the time of each administration and any possible side effect or adverse event.

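### Two 1-cm hair segments cut at T4 are said to represent three periods; they cannot separate them, and at about 1 cm per month the older segment straddles trauma and treatment

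*Protocol article*

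**What the plan says.** All of this is in the protocol article.

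- Neuroendocrine measures, on sampling: "Fifteen mg of hair is collected at T4". No other hair collection is described.
- Same section, on what is analysed and what it stands for: "Focus will be on the first 2 1 cm segments of scalp-nearest samples, representing the month prior to trauma, the month after the intervention".
- The same sentence then names a third period: "and a time period in between".
- Study procedures, on the timing of T4: "One month after the end of the intervention (T4) (i.e. approximately 1.5 month post-trauma".
- Intervention, on the first dose: "at the latest on day 10 post-trauma exposure (T2".
- Abstract, on the length of treatment: "Participants will be randomized to 7.5 days of intranasal oxytocin (40 IU) or placebo twice a day".

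The article gives no hair growth rate, no third segment and no rule that assigns segments to periods. The stated purpose of the hair measure is only to look back at cortisol levels. The section on secondary outcomes and exploratory analyses plans linear mixed models for change in neuroendocrine measures across the intervention, without mentioning hair.

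**The concern.** The count does not match: two segments, three periods. The calendar does not fit either. If T4 is about 1.5 months after trauma, the start of the month before trauma lies about 2.5 months back, and 2 cm of hair reaches that far only if hair grows slowly.

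Hair is the only measure in the trial that could look at HPA activity before the trauma, since all saliva and blood samples are taken afterwards. The Background names pre-existing HPA dysregulation as a risk factor for PTSD, so a pre-trauma value would be of interest. If the older segment were taken as that value when part of it was laid down after the trauma or during treatment, it would be no baseline. The article itself expects oxytocin to act on the HPA axis, so the contamination could differ between the arms.

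**Working it through.** **Inputs from the article.** Hair cut at T4 only; two 1-cm segments; treatment lasts 7.5 days; first dose by day 10; T4 is one month after treatment ends.

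**Assumptions.** One month = 30 days. Growth rate g = 1 cm per month as base case, inferred from the pairing of 1-cm segments with months; range 0.8 to 1.2. The article gives no earliest start day, so days 3 and 4 are used as examples.

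**Step 1: reproduce the stated timing of T4.** T4 = start day + 7.5 + 30.
- Start day 10: 10 + 7.5 + 30 = day 47.5, or 47.5/30 = 1.58 months.
- Start day 3: 3 + 7.5 + 30 = day 40.5, or 1.35 months.

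Both agree with the article's approximate 1.5 months.

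**Step 2: count.** Two segments yield two cortisol values. Three periods need three values. This holds whatever the growth rate.

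**Step 3: place the segments.** One centimetre spans 30/g days. Segment 1 runs from T4 − 30/g to T4; segment 2 from T4 − 2 × 30/g to T4 − 30/g. Day 0 is the trauma. For a day-10 start (treatment from day 10 to day 17.5):

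| g (cm/month) | Days per cm | Segment 1 (days) | Segment 2 (days) | Pre-trauma share of segment 2 | Treatment days in segment 2 |
|---|---|---|---|---|---|
| 0.8 | 37.5 | 10 to 47.5 | −27.5 to 10 | 27.5/37.5 = 73% | 0 |
| 1.0 | 30 | 17.5 to 47.5 | −12.5 to 17.5 | 12.5/30 = 42% | 7.5 |
| 1.2 | 25 | 22.5 to 47.5 | −2.5 to 22.5 | 2.5/25 = 10% | 7.5 |

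**Step 4: earlier starts at 1 cm per month.**
- Day 4: T4 = 41.5; segment 2 = −18.5 to 11.5; 18.5/30 = 62% pre-trauma.
- Day 3: T4 = 40.5; segment 2 = −19.5 to 10.5; 19.5/30 = 65% pre-trauma.

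With a 30.44-day month the day-10 and day-3 shares become 43% and 66%. At 1 cm per month the boundary between the segments always falls at the end of treatment, because T4 is set one month after it. Segment 2 then holds the whole course for each of these start days.

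**Step 5: length of hair needed.** At 1 cm per month, reaching the start of the month before trauma takes (T4 + 30)/30 cm: 77.5/30 = 2.58 cm for a day-10 start and 70.5/30 = 2.35 cm for day 3. Two centimetres fall short in both cases.

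**Step 6: where the picture changes.**
- No treatment days in segment 2: 30/g ≥ 7.5 + 30 = 37.5, so g ≤ 0.8, whatever the start day.
- Two segments reach the full month before trauma: 2 × 30/g ≥ T4 + 30, so g ≤ 60/77.5 = 0.77 (day 10) or 60/70.5 = 0.85 (day 3).
- Segment 2 wholly pre-trauma: 30/g ≥ T4, so g ≤ 30/47.5 = 0.63 (day 10) or 30/40.5 = 0.74 (day 3). Segment 1 then spans trauma, treatment and follow-up together.

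**Step 7: a third segment.** At 1 cm per month and a day-10 start it covers about day −42.5 to −12.5. It is wholly pre-trauma as long as 2 × 30/g ≥ 47.5, that is g ≤ 60/47.5 = 1.26.

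**The case against.** **The growth rate is not in the article.** This stands. The 1 cm per month is an inference from the wording, and every day range depends on it. The count mismatch does not.

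**The two segments may be meant as one continuous window with a mixed middle.** That reading removes the count problem. At 1 cm per month it still leaves roughly a third to over half of the pre-trauma month uncovered, and it gives no separate pre-trauma value.

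**Allocating segments to periods is assay detail that an article may leave to the full protocol.** That would excuse silence. Here the article does state an allocation, and the allocation does not work.

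**The trial has other pre-intervention HPA measures.** True: resting salivary cortisol and DHEAS at T2, plus the awakening curve and dexamethasone suppression test before dosing. Comparing the arms on segment 1 also needs no hair baseline. These measures cover the time before treatment, but not before trauma.

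**Stronger readings that the article does not support.**
- A reader might infer that segment 2 always contains the full treatment course. At 0.8 cm per month or slower it contains none of it.
- A reader might infer that segment 2 can never be a clean pre-trauma value. At about 0.63 to 0.74 cm per month or slower it would be, at the price of a mixed segment 1.
- A reader might infer that the planned hair-cortisol comparison is biased by adjusting for a post-randomisation value. The article names no such adjustment. Hair cortisol is not among the listed moderators, gender and age are the named confounders, and no hair segment is called a baseline.

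**Conclusion.** The stated mapping is wrong as written: two segments cannot give separate values for three periods. That conclusion needs no outside figure.

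That segment 2 misses much of the pre-trauma month and contains the trauma and the treatment course holds at about 1 cm per month. Its pre-trauma share is then 42% for a day-10 start and 62% to 65% for a start on day 4 or 3. Over the assumed range of 0.8 to 1.2 cm per month with a day-10 start it varies from 73% to 10%, and the treatment days leave segment 2 at the slow end.

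The harm is conditional. If segment 2 entered the planned models of neuroendocrine change as the value before the intervention, it would, at about 1 cm per month, be partly a post-randomisation measure. The article does not say that it will. Hair cortisol is not the primary outcome; the CAPS comparison at T4 and the sample size are untouched. The point should be corrected, but it does not threaten the trial's main result.

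**What to change.** State the assumed growth rate, then do one of the following.

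1. **Relabel.** Call segment 1 the post-intervention period. Call segment 2 a mixed period (before and around the trauma, and treatment), and say that it will not serve as a baseline, covariate or moderator. Drop the claim to represent the month before trauma. This costs nothing beyond the text change.
2. **Assay a third 1-cm segment** as the pre-trauma value, with segment 2 as the in-between period. At 1 cm per month and a day-10 start, the third segment is a pre-trauma month but not the one immediately before the event, and the label should say so. This adds laboratory cost and loses participants with short hair. The article gives the sample mass (15 mg) but no lock length, so whether a third segment exists or yields enough material has to be checked with the laboratory first.

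If three segments were intended all along and the number two is a slip, correct the number and add the same labels.

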### (Epi)genetics

To investigate possible effects of genetic variation on the effectiveness of oxytocin treatment, we will assess carrier status of single-nucleotide polymorphisms (SNPs) which have previously been related to PTSD symptoms and/or dysregulated biological systems in PTSD (e.g. OXTR, glucocorticoid receptor, FKBP5). Furthermore, DNA methylation of CPG-islands of these genes (i.e. epigenetics) will be assessed. Through DNA methylation, environmental experiences regulate gene expression, which may induce lasting changes in stress reactivity [91,92]. Differential levels of DNA methylation of genes related to stress reactivity have already been associated with PTSD and early life stress [93-95]. These measures will be used for exploratory subgroup analyses of the effects of the intervention. For the collection of (epi)genetic material 6 ml of whole blood is collected in an EDTA tube, which is kept at 7°C until DNA is extracted and stored by a certified laboratory.

#### Statistical analysis - primary outcome

To assess the efficacy of the oxytocin intervention, we will analyze the difference in mean CAPS scores between the 2 arms of the trial at 1.5 month post-trauma (T4). Descriptive statistics will be used for exploration of the data. All analyses will be conducted on the basis of intention-to-treat (ITT). Results will be expressed as differences in mean scores between the 2 groups with 95% confidence intervals**.** P-values <0.05 will be considered to indicate statistical significance.

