### Study design

The ‘BONDS’ study is a multicenter double-blind randomized placebo-controlled trial in recently traumatized ED patients with increased risk of PTSD. The study design was set up with 2 baseline assessments (T1-T2) and 4 post-intervention assessments (T3-T6) (Figure 1). Participants will be randomly assigned to 1 of the 2 intervention groups, stratified by gender, ensuring that both genders are equally distributed over the 2 intervention groups.

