#### Statistical analysis - secondary outcomes and exploratory analyses

Additionally, we will analyze the difference in mean CAPS scores between the 2 arms of the trial at 3 (T5) and 6 (T6) months post-trauma. We will investigate the difference in levels of depression and other psychopathology symptoms between the 2 trial arms during the follow-up assessments. Changes in continuous symptom and physiological and neuroendocrine measures between groups from pre- to post-intervention will be evaluated by longitudinal analyses using linear mixed models. In multivariate analyses we will investigate potential confounding factors, such as gender and age. Based on earlier studies on early interventions to prevent PTSD [12] and on different interindividual responses to intranasal oxytocin administration [51,52] relevant exploratory subgroup comparisons will be made to examine whether treatment effects differ between specific subgroups. We will analyze if variables such as subjective social support, attachment, coping style, (epi)genetics, peritraumatic dissociation, and history of childhood trauma, moderate the effect of the intervention on our outcome measures.

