#### Sample size calculation

Sample size calculation was based on the minimal effect size considered to be clinically relevant in the prevention of PTSD symptom development and on previous results of studies on the effects of long-term oxytocin administration in reducing psychiatric symptoms. We used the program NQuery Advisor® 7.0 [96] to calculate minimal group sizes. A previous study in a similar population by our department has shown that we can expect a standard deviation between 19.93-23.81 points on the CAPS score at approximately 1 month after trauma [60]. Based on a SD of 23.81, a small-to-medium effect size of d = 0.4 would result in a 9.52-point lower CAPS score in the oxytocin-treated group compared to the placebo group at 1 month post-intervention (a CAPS score of 45 is required for a PTSD-diagnosis). We consider this group difference on the CAPS to be clinically relevant.

Support for the notion that an effect size of d = 0.4 adequately reflects the potential of oxytocin to reduce psychiatric symptoms stems from 2 previous studies on long-term intranasal oxytocin administration in the treatment of positive and negative symptoms in schizophrenia patients [61,97]. The observed effect sizes were between d = 0.05 - 0.88 [97] and d = 0.24 -.74 (for most outcomes around d = 0.4) [61], depending on the outcome measure. Noteworthy, oxytocin treatment greatly reduced anxiety symptoms in schizophrenic patients (d = 0.62) [97].

To be able to detect a group difference with an effect size of d = 0.4 using a two sample t-test with an alpha of 0.05 two-sided significance level and power of 80%, 100 participants per trial arm are needed. To allow for 10% attrition (estimated from our previous study in a similar population) we will include 110 participants in each study group at T1. Therefore we will include 220 participants in total.

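### The primary T4 CAPS comparison, as described, leaves baseline severity and the gender stratum to secondary analyses and so gives up precision that is free to recover

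*Protocol article*

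**What the plan says.** - **Primary analysis** (Statistical analysis - primary outcome): "we will analyze the difference in mean CAPS scores between the 2 arms of the trial at 1.5 month post-trauma (T4"), and "Results will be expressed as differences in mean scores between the 2 groups with 95% confidence intervals". No test, model or covariate is named.
- **Sizing** (Sample size calculation): the calculation is made "using a two sample t-test with an alpha of 0.05 two-sided significance level and power of 80" per cent. Its inputs are given as "Based on a SD of 23.81, a small-to-medium effect size of d = 0.4 would result in a 9.52-point lower CAPS score", and the result is "power of 80%, 100 participants per trial arm are needed". No reduction in variance from a baseline covariate is counted.
- **Randomisation** (Study design): allocation is "stratified by gender, ensuring that both genders are equally distributed over the 2 intervention groups".
- **Baseline** (Study procedures): before randomisation, the T1 visit is used to "collect baseline characteristics (i.e. current PTSD symptoms, history of and current other psychopathologies" and other items. Only participants found eligible at T1 are randomised.
- **Covariates** (Statistical analysis - secondary outcomes and exploratory analyses): "In multivariate analyses we will investigate potential confounding factors, such as gender and age". The same section plans linear mixed models for pre-to-post change in continuous symptom measures.

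**The concern.** The article does mention covariates and baseline modelling, but places both outside the primary comparison. Two pieces of information available for every randomised patient at no extra cost, T1 severity and gender, therefore play no described part in the primary estimate.

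Three things follow:
- If T1 severity predicts T4 severity, leaving it out gives a wider confidence interval and lower power from the same 220 patients.
- Stratifying by gender removes gender imbalance from the true sampling variation of the treatment difference. A plain t-test still counts the between-gender variance in its standard error, so that standard error is somewhat too large.
- Gender and age are called confounding factors. In a randomised treatment comparison they are prognostic factors, and gender is also balanced by design. Their role is prespecified adjustment for precision.

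**Working it through.** **Inputs from the article (Sample size calculation).** d = 0.4; SD 23.81 (upper end of a stated range from 19.93); difference 0.4 × 23.81 = 9.52 points; two-sided alpha 0.05; power 80%; 100 per arm, raised to 110 for 10% attrition.

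**Inputs assumed.** The correlation r between baseline and T4 CAPS is not given; 0.2 to 0.7 is used. The gender difference in T4 CAPS is not given; 0.3 to 0.5 within-gender SD with an equal gender split is used.

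**Step 1: reproduce the stated figure.** The normal approximation gives 99 per arm. Exact (noncentral t) power is 80.0% at 99 per arm and 80.4% at 100. After 10% attrition, 110 × 0.9 = 99 per arm remain, again 80.0%. The stated size reproduces.

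**Step 2: unadjusted precision.** Half-width = 1.96 × 23.81 × √(2/100) = 6.60 points.

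**Step 3: adjust for baseline.** Residual SD = 23.81 × √(1 − r²). Effective d = 9.52 / residual SD. Half-width = 1.96 × residual SD × √(2/100). Power is from the noncentral t with 197 df. The unadjusted size per arm with the same precision is 100 / (1 − r²).

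| Assumed r | Residual SD | Effective d | Power, 100 per arm | 95% CI half-width | Equivalent unadjusted n per arm |
|---|---|---|---|---|---|
| none (unadjusted) | 23.81 | 0.400 | 80.4% | 6.60 | 100 |
| 0.2 | 23.33 | 0.408 | 81.9% | 6.47 | 104 |
| 0.3 | 22.71 | 0.419 | 83.9% | 6.30 | 110 |
| 0.5 | 20.62 | 0.462 | 90.1% | 5.72 | 133 |
| 0.7 | 17.00 | 0.560 | 97.6% | 4.71 | 196 |

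At the lower stated SD of 19.93, unadjusted power for 9.52 points is already 91.9%; at r = 0.5 it becomes 97.3%.

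**Step 4: the gender stratum.** With gender balanced across arms and a gender difference of δ within-gender SD, the t-test's standard error is too large by a factor √(1 + 0.25δ²).
- δ = 0.3: √1.0225 = 1.011, so a nominal 5% test has a true type I error of about 4.7%.
- δ = 0.5: √1.0625 = 1.031, true type I error about 4.3%.

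The factor 0.25 comes from the equal gender split.

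**The case against.** The strongest reply is that the article never says the comparison is unadjusted. A covariate-adjusted model also yields a mean difference with a 95% CI, and sizing on a t-test does not bind the analysis. This is a condensed article, the statistical analysis plan is not shown, and covariate lists are often left to that plan. This stands in part: 'unadjusted' is an inference. But the article is not simply silent. It names gender, age and pre-to-post modelling and puts them under secondary and exploratory analyses, so a reader would take the primary comparison to be without them.

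Other objections also carry weight:
- **The gain is assumed.** At r = 0.2 it is only about 1.5 percentage points of power. Entry is restricted to patients above the TSQ or PDI cut-off, which could narrow the baseline range and lower r.
- **The T1 instrument is inferred to be the CAPS.** The inference is strong: the article assesses PTSD symptoms with the CAPS and uses the MINI for other disorders and lifetime PTSD. But Study procedures does not name the T1 instrument, and the flowchart is not shown.
- **Baseline is not ignored altogether.** The secondary mixed models use it.

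A reader might infer that covariates will be picked after inspecting the data. The article does not say that; its wording is loose and concerns secondary analyses. A reader might also infer that chance baseline imbalance biases the primary estimate. It does not: the difference in means is unbiased under randomisation, and its interval already allows for such imbalance. Adjustment makes that interval narrower.

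**Conclusion.** The point holds as one of efficiency. Read together, the analysis and sample size sections describe a primary comparison that uses neither baseline severity nor the stratification factor. The cost ranges from minor (about 1.5 points of power at r = 0.2) to substantial (about 10 points at r = 0.5 and 17 at r = 0.7), and the document does not show where in that range the trial lies. The loss from omitting gender is small and in the conservative direction.

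It would be wrong to conclude that the trial is underpowered or its primary test invalid. The t-test reaches its own 80% target with the stated inputs, and neglecting the stratum makes the test slightly cautious, not liberal. The conclusion rests on 'unadjusted' being the natural reading, on the T1 score being the CAPS, and on the assumed correlation and gender difference. The change is worth making because it costs almost nothing.

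**What to change.** 1. In Statistical analysis - primary outcome, state that the T4 CAPS difference is estimated by a linear model with treatment, baseline (T1) PTSD severity (CAPS) and gender as prespecified covariates. Report the adjusted mean difference with its 95% CI and p-value.
2. Keep the unadjusted difference in means as a sensitivity analysis.
3. In Statistical analysis - secondary outcomes and exploratory analyses, describe gender and age as prespecified prognostic covariates for treatment comparisons, not as confounding factors to be investigated.
4. Leave the sample size unchanged; any gain from adjustment serves as reserve.

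If the statistical analysis plan already specifies such a model, align the article with it. The cost is two or three sentences, with no new data and no additional patients.

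### The primary T4 CAPS comparison, as described, leaves out baseline PTSD severity and the gender stratum; adjusting for both would add precision at almost no cost

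*Protocol article*

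**What the plan says.** All references are to the Protocol article.

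- **Statistical analysis - primary outcome:** "we will analyze the difference in mean CAPS scores between the 2 arms of the trial at 1.5 month post-trauma (T4"). The result is a mean difference with a 95% confidence interval, on the principle that "All analyses will be conducted on the basis of intention-to-treat (ITT"). The section names no test or model.
- **Sample size calculation:** the test appears only here: "using a two sample t-test with an alpha of 0.05 two-sided significance level and power of 80%, 100 participants per trial arm are needed". The target is given as "Based on a SD of 23.81, a small-to-medium effect size of d = 0.4 would result in a 9.52-point lower CAPS score", and the loss allowance as "To allow for 10% attrition (estimated from our previous study in a similar population) we will include 110 participants in each study group at T1".
- **Statistical analysis - secondary outcomes and exploratory analyses:** changes in continuous symptom and biological measures "from pre- to post-intervention will be evaluated by longitudinal analyses using linear mixed models". Gender and age are listed in the same section, as potential confounders for multivariate analyses.
- **Abstract (Methods/Design) and Study procedures:** PTSD symptom severity is collected before treatment starts, at T1, and again at T4, T5 and T6.
- **Study design:** randomisation is stratified by gender.

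**The concern.** PTSD severity soon after trauma is likely to predict severity a few weeks later. The trial records it before treatment, yet the primary comparison as described uses T4 scores alone. It also leaves out gender, although an analysis should normally reflect the factor used to stratify randomisation. The method that could use both is listed only for secondary questions.

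Two things are at stake. The first is precision: the unadjusted contrast has a wider interval than the collected data allow, in a trial planned at 80% power whose Strengths and limitations section calls recruitment challenging. The second is protection against selective loss. Avoidance is one of the CAPS symptom clusters, so attendance at T4 could depend on severity. If that dependence differs between arms and runs through baseline severity, adjusting for baseline corrects it and a raw mean difference does not.

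**Working it through.** **Inputs from the Sample size calculation section:** d = 0.4, SD 23.81, difference 9.52, two-sided alpha 0.05, power 80%, 100 per arm raised to 110 for 10% attrition.

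**Assumed, because the article gives no figure:** the correlation r between T1 and T4 CAPS, taken as 0.3, 0.5 and 0.7. Screening on risk scores may narrow the range of baseline severity and lower r, so 0.3 should be taken seriously. It is also assumed that T1 severity is measured with the CAPS. Study procedures does not name the T1 instrument, but the CAPS is the interview the article describes for PTSD symptoms.

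**1. The plan's own figures reproduce.**
- Difference: 0.4 × 23.81 = 9.52.
- Normal approximation: n per arm = 2(1.96 + 0.842)² / 0.4² = 98.1, so 99. The exact t-test calculation gives 99.08, so 100.
- Attrition: 99 / (1 − 0.10) = 110 per arm, 220 in total.
- If 10% of 220 (22 people) lack a T4 CAPS, 198 remain, or 99 per arm. Power is then 79.97% by t-test (80.4% by normal approximation). The loss is already budgeted.

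**2. Standard error with and without baseline.**
- Unadjusted: 23.81 × √(2/99) = 3.38.
- Adjusted: 3.38 × √(1 − r²).

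**3. Power, from Φ(9.52/SE − 1.96).**

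| r | SE | 9.52/SE | Power |
|---|---|---|---|
| unadjusted | 3.38 | 2.81 | about 80% |
| 0.3 | 3.23 | 2.95 | about 84% |
| 0.5 | 2.93 | 3.25 | about 90% |
| 0.7 | 2.42 | 3.94 | about 98% |

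**4. Where the gain comes from.** If all 220 contributed T4 information to an unadjusted comparison, t-test power would be 84.0%. That is an upper bound, because a model or imputation recovers only part of what is lost. At r = 0.5, adjusting the 198 for baseline gives more than that.

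**5. Bias from missing T4 scores.** The bias in one arm's mean is the fraction missing times the gap between its missing and observed participants.
- 10% missing, gap 9.52, one arm only: 0.95 points.
- 10% missing, gap of one SD, one arm only: 0.10 × 23.81 = 2.38 points, a quarter of the 9.52 target.
- Equal loss and the same gap in both arms: zero bias in the difference.
- 15% against 5% missing, the same one-SD gap: (0.15 − 0.05) × 23.81 = 2.38 points.

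**6. Simulation.** 600 trials of 220 participants were simulated, with a true effect of −9.52, 9.8% missing T4, a T1–T4 correlation of 0.5, and loss driven by baseline CAPS in opposite directions in the two arms. Mean estimates:
- unadjusted comparison of attenders: −7.55 (1.97 / 9.52, about 20% too small);
- baseline-adjusted ANCOVA in the same attenders: −9.61;
- mixed model with a common baseline mean: −9.63.

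With loss completely at random, the standard deviations of the estimates were 3.42, 2.94 and 2.93. ANCOVA in attenders and the mixed model are almost identical in both scenarios, so nearly all the benefit here comes from using baseline.

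**The case against.** A reader might infer that the primary analysis is confined to T4 attenders and so breaks the intention-to-treat promise. The article does not support that. The primary-outcome section names no test and restricts no one. The t-test is named only to size the trial, and imputation or a likelihood model would also yield a T4 mean difference. Handling of missing T4 scores may sit in an analysis plan or full protocol not shown here, so the article's silence is no finding. The 10% is a planning allowance counted at T1, before randomisation, and not a stated rate of missing T4 CAPS among those randomised.

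A reader might also take the 20% bias as what to expect. It needs loss that depends on severity in opposite directions by arm, a deliberately adverse pattern. Without a difference between arms in how loss relates to severity, the bias is nil. Nor is it a contradiction to have a longitudinal model beside a single-visit primary contrast; that is ordinary design. An unadjusted comparison is valid under randomisation, and its power is already close to 80%.

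All of this stands. It does not answer the narrower point. The article does describe its primary contrast, and it places baseline-to-follow-up modelling and gender among the secondary analyses. On that description, a better estimator built from data already collected is left out of the primary question.

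**Conclusion.** The point holds as an improvement to the stated primary method; the plan is not in error. As described, the primary contrast omits baseline PTSD severity and the stratification factor. With 99 per arm, adjusting for baseline cuts the standard error from about 3.38 to 2.93 and raises power from about 80% to 90% if the T1–T4 correlation is 0.5. At 0.3 the gain is smaller, to about 84%. These figures rest on the assumed correlation, on CAPS being measured at T1, and on the planned SD and effect. No size is given for gender, because the article has no figure for its relation to CAPS.

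Adjustment also removes bias from loss that depends on baseline severity, provided the model for baseline is adequate. It would not by itself remove bias from loss that depends on unobserved T4 severity. Required sample size is unaffected.

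**What to change.** In the primary-outcome section, name the primary estimate as the T4 treatment contrast in CAPS adjusted for baseline CAPS and gender. Preferably take it from the linear mixed model already planned, fitted to CAPS at T1, T4, T5 and T6 in all randomised participants with any CAPS. Report the unadjusted T4 mean difference with its 95% confidence interval as supportive. ANCOVA of T4 CAPS on baseline and gender is a simpler alternative with nearly the same precision in the simulation.

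The cost is a change of wording, made before unblinding. No new data, visits or participants are needed, and the sample size calculation can stand as a conservative one. If the unseen analysis plan already adjusts in this way, the article's description only needs to be aligned with it. Sensitivity analyses for missing T4 scores, and follow-up after withdrawal from treatment, may also be covered there and are not part of this point.
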